### Statistical analysis plan

Hypothesis testing for this study will be based on a superiority framework and will be conducted at the α = 0.05 significance level. Primary analyses will be conducted using a complete-case, intention-to-treat approach, where participants will be analyzed in the trial arm their cluster was randomized to, irrespective of contamination or adherence to instructions on how to use the iNCK. The unit of analysis will be the individual neonate (neonatal mortality, omphalitis, fever, hypothermia, and healthcare utilization for newborn morbidities) or the individual woman (PPH and healthcare utilization for PPH). Risk ratios for the primary (neonatal mortality) and secondary (omphalitis and PPH) outcomes will be estimated using multivariable modified Poisson regression [29], with generalized estimating equations to account for the clustered design and robust variance estimators to account for multiple births and/or multiple pregnancies during the study period. Analyses of neonatal mortality (the primary outcome) will adjust for newborn sex, antenatal care, and gestational age at birth to improve power and efficiency; calendar time to account for underlying temporal trends (defined as month of birth, setting month of study launch as month 0); and the covariates used in the randomization procedure: GB study district, log cluster-specific baseline NMRs, and the cluster-specific baseline proportion of children delivered at a health facility. Analyses of omphalitis (secondary outcome) will adjust for newborn sex, antenatal care, and GB study district. Analyses of PPH (secondary outcome) will exclude women who delivered via C-section, and will adjust for parity, maternal age, history of prior C-section, history of prior PPH, GB study district, and the cluster-specific baseline proportion of women who reported experiencing PPH. The frequency of hypothermia, cold stress, and fever detected by ThermoSpot™ within the first 14 days of life will be described amongst participants in intervention clusters only, overall and by calendar month to assess seasonality. Finally, the frequency and location of health facility utilization for omphalitis, PPH, hypothermia, and fever will be described using counts and proportions amongst individuals experiencing each respective morbidity and will be stratified by trial arm. The proportion accessing healthcare services by trial arm will be compared using clustered t-tests and modified Poisson regression.

Subgroup analyses will examine primary and secondary outcomes by place of delivery, GB district, newborn sex, gestational age at birth, the timing of intervention delivery relative to the date of birth, and the frequency of postnatal LHW home visits (Table 2). For analyses of neonatal mortality, omphalitis, and PPH, interaction terms between trial arm and each subgroup or process indicator will be analyzed in separate models. We will also describe compliance to the iNCK package and its components among intervention arm participants, including overall uptake as well as the timing and duration of usage. In secondary, per-protocol analyses of the primary and secondary outcomes, intervention arm participants will be assigned compliance scores using an algorithm defined in Supplemental Tables 1 and 2. Participants scoring at or above thresholds of compliance (e.g., 60%, 70%, 80%, 90%, and 100%) will be propensity-score matched to participants in control clusters, and modified Poisson regression will be used as above to compare good compliers with their matched unexposed participants. Finally, we will conduct supplementary analyses of the primary neonatal mortality outcome using alternative mortality definitions (i.e., death on day 1, days 1–7, days 8–28, days 2–7, and days 2–28).

Cause of death will be ascertained using VA data using previously described methods and will also inform the primary analysis by differentiating stillbirths from early neonatal deaths [30]. Stata version 17.0 or newer will be used for all analyses.

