For the intervention phase of the trial, data collectors will complete one in-person at-home visit, a mid-point assessment call, and try for a second in-person at home visit. The first in-person visit will occur during the third trimester of pregnancy, at which time data collectors will screen potential participants for eligibility. If eligibility criteria are met, participants who provide informed consent to participate in the trial will receive a pictorial diary from the LHW to enable self-reporting regarding compliance for individual iNCK components (intervention clusters only). Data collectors will then administer a questionnaire in the form of a structured interview to collect sociodemographic and household data. On the 8^th^ day of a newborn's life, field supervisors will attempt to complete phone interviews with participant households to collect information surrounding the baby's delivery and study outcomes of interest that may have occurred during the first week of the newborn’s life. While efforts will be made to complete these calls on the 8th day of life, a one-week window will be permitted for completing this phone call (between the 8th day through the 14th day of the newborn’s life). If the study team is unable to contact the participant for this data collection touchpoint, data collectors will obtain this information during the in-person at-home visit on the 29th day of the baby’s life. Data collectors will visit participant households on day 29 of the newborn's life to collect information that will enable the assessment of primary and secondary outcomes related to neonatal and maternal health, and will collect the completed pictorial diaries and any unused misoprostol tablets from the participants before leaving. While efforts will be made to collect data on day 29, this in-person visit will be attempted up until day 43 post-natal age, if necessary. If, after two to three consecutive visits, the study team cannot reach a participant household by day 43, the day 29 questionnaire may be completed over the phone by the field supervisor that presides over the districts in which these participants live. However, if a participant cannot accommodate the time required to complete the questionnaires involved with the day 29 visit by phone or in person before or on day 43 of the newborn’s life, or if the participant is lost to follow-up following the notification of birth, a modified vital outcomes questionnaire will be administered to participants, if possible, either in-person or over the telephone, to confirm whether their baby survived the neonatal period.

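### The primary mortality model omits maternal age, parity and multiple birth, which the trial holds and which are settled before the kit visit; adding them would give modest protection against enrolment differences

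*Protocol article*

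**What the plan says.** The Statistical analysis plan section of the protocol article names the covariates of the primary model. At the individual level: "Analyses of neonatal mortality (the primary outcome) will adjust for newborn sex, antenatal care, and gestational age at birth to improve power and efficiency". To these it adds month of birth and the covariates used in the constrained randomization, namely district, log baseline cluster neonatal mortality rate and baseline cluster share of facility deliveries.

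Multiple births appear only in the variance: the plan uses "robust variance estimators to account for multiple births and/or multiple pregnancies during the study period". For PPH, the same section says that the analysis "will adjust for parity, maternal age, history of prior C-section, history of prior PPH", together with two further terms. The trial therefore holds maternal age and parity, and can tell multiple births from singletons.

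On timing, Data collection and data management says that at the third-trimester visit data collectors "administer a questionnaire in the form of a structured interview to collect sociodemographic and household data". The day-8 call is used to "collect information surrounding the baby's delivery and study outcomes of interest", with the day-29 visit as fallback. Study design says that women are identified and approached after cluster randomization, and that data collectors know the allocation.

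**The concern.** In a cluster trial that recruits after open allocation, randomization balances clusters but not the individuals who are later found and consented. The constrained randomization here controls three cluster-level quantities, and none of them describes the mix of mothers enrolled. If the arms end up with different shares of first births, older mothers or twins, the difference goes into the risk ratio unless the model contains those factors. A robust variance makes the standard error honest about correlated siblings, but it does not remove a difference in twin share from the point estimate.

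Maternal age, parity and plurality are settled before the kit is handed over, so adjusting for them is safe: none can lie on the path from kit to survival. At stake is some protection against measured recruitment imbalance, and a little precision, from data that the trial already holds.

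**Working it through.** **Inputs from the article.** Sample size: 39 clusters per arm, 306 live births per cluster, 23,868 in total, 35 deaths per 1,000 in control, a 25% relative reduction (to 26.25 per 1,000), intracluster correlation (ICC) 0.002, 80% power. Statistical analysis plan: alpha 0.05, taken here as two-sided.

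**Assumed inputs.** The article gives no prevalence or risk ratio for the omitted factors.
- Multiple births: 2 to 4% of newborns, with a risk ratio for death of 3 to 6.
- An age or parity risk group: 25 to 30% of mothers, with a risk ratio of 1.3 to 2.0.
- Arm differences: 0.5 to 1 percentage point in multiple births; 3 to 5 points in the age or parity group.

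**1. The plan's own power figure.** The two-proportion formula gives 6,086 newborns per arm without clustering. The design effect is 1 + 305 × 0.002 = 1.61. With 39 × 306 = 11,934 per arm, the effective size is 11,934 / 1.61 = 7,412, and power is 87.1%. The stated 80% is not reproduced from the stated inputs. An ICC of about 0.00315 gives it: design effect 1.961, effective size 6,086. That mismatch is a separate matter, so both baselines are carried forward.

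**2. Outcome variance explained by an omitted binary factor.** With share s, risk ratio RR and mean risk p = (0.035 + 0.02625) / 2 = 0.030625:

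R² = s(1 − s)(r1 − r0)² / [p(1 − p)], where r0 = p / [1 + (RR − 1)s] and r1 = RR × r0.

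| Factor | r1 − r0 | R² |
|---|---|---|
| Multiple birth, 2%, RR 3 | 0.0589 | 0.23% |
| Multiple birth, 4%, RR 6 | 0.1276 | 2.11% |
| Age or parity, 25%, RR 1.3 | 0.0085 | 0.05% |
| Age or parity, 30%, RR 2 | 0.0236 | 0.39% |

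The sums run from about 0.28% to 2.5%; a joint range of 0.2 to 3% covers them.

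**3. Power after adding the covariates.** The cautious version removes R² only from the within-cluster part of the design effect; the generous version removes it from the whole variance.

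| Baseline | R² 0.2% (cautious / generous) | R² 3% (cautious / generous) |
|---|---|---|
| 80.0% (ICC 0.00315) | 80.05% / 80.08% | 80.6% / 81.2% |
| 87.1% (ICC 0.002) | 87.16% / 87.18% | 87.7% / 88.1% |

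On the generous version the gain is about 0.1 to 1.2 points, worth 0.002 × 23,868 = 48 to 0.03 × 23,868 = 716 births.

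**4. Shift in the unadjusted risk ratio.** If the factor has share a in one arm and b in the other, the risk ratio is multiplied by [1 + b(RR − 1)] / [1 + a(RR − 1)].
- Multiple birth, 2.0% against 2.5%, RR 3: 1.05 / 1.04 = 1.010.
- Multiple birth, 2% against 3%, RR 6: 1.15 / 1.10 = 1.045.
- Age or parity, 25% against 28%, RR 1.3: 1.084 / 1.075 = 1.008.
- Age or parity, 25% against 30%, RR 2: 1.30 / 1.25 = 1.040.

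For scale, a 4% shift against the kit would turn the target risk ratio of 0.75 into 0.75 × 1.04 = 0.78.

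**5. How likely is the assumed difference in multiple births?** Doubling the variance for pairing, the standard error of a difference in share is √[4q(1 − q) / 11,934], with q the mean share. For 2.0% against 2.5% it is 0.0027, so the difference is 1.8 standard errors. For 2% against 3% and 3% against 4% the difference is 3.5 and 3.0 standard errors. Between-cluster variation is ignored.

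Steps 2 to 4 are marginal: they treat each factor as if the model held nothing else.

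**The case against.** The strongest reply is that this is a preference about covariates. The plan prespecifies a coherent model, the estimator is valid without these terms, and using age and parity for a maternal outcome creates no duty to use them for a newborn one. That stands: nothing here is wrong or contradictory.

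Several further objections also stand and reduce the point.
- **Gestational age is already adjusted for.** Whatever part of the twin risk runs through early birth is already in the model. The multiple-birth figures above are therefore upper figures.
- **The imbalances are assumed.** A full point in multiple births is about 3 standard errors or more, so selection would largely have to produce it, and nothing in the article says that plurality is known at enrolment. Recruitment is also meant to be broad: Lady Health Workers register all pregnancies in their area and the eligibility rule is simple.
- **Recording at the kit visit is not documented.** A reader might infer that all three variables are collected before the kit is given. The article supports less: they are determined by then and held in the trial data. Plurality is probably captured with the delivery information.
- **Missing values may not be innocent.** Families reached only by the short vital-outcomes questionnaire may lack plurality, so its absence would go with incomplete follow-up.

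A reader might also infer that the model contains no maternal characteristic. It does, because antenatal care is one. These objections shrink the claim but do not remove it: none shows that adding the terms, with a rule for missing values, would do harm.

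**Conclusion.** The point holds as a minor improvement. The published covariate list leaves out three pre-kit factors that the trial holds, in a design where women are enrolled after open allocation. The main reason to add them is protection against measured differences in enrolment: roughly 1 to 4% on the unadjusted risk ratio under the assumed shares, risk ratios and arm differences, and less for multiple birth. Unmeasured differences would remain.

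Precision is a weak reason. It would be tempting to say that the plan gives up useful power at no cost, but a gain of at most about 0.1 to 1.2 points does not support that. Nor do the documents support reading the omission as a bias already present, since no arm difference is reported, or extending the point to multiple birth in the PPH model, for which no size can be shown.

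**What to change.** Prespecify maternal age, parity and multiple birth as additional covariates in the primary mortality model. Define parity as at enrolment, and multiple birth by the plurality of the pregnancy (counting a stillborn co-twin), so that both remain pre-kit factors.

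Add a simple rule for missing values of these terms, such as a single imputed value set without reference to arm or outcome, or a missing category. Then no newborn with known vital status is lost through the complete-case approach because of the added covariates. Report by arm how many newborns the rule touches, and show the result from the published covariate list beside it. Settle the wording before anyone choosing covariates sees outcomes by arm.

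The cost is a few lines of analysis-plan text and a few extra parameters, with no new data or enrolment. The downside is that plurality may be missing where only the vital-outcomes questionnaire was completed, which is why those counts should be reported.

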### Study design

This study is a pragmatic, open-label, community-based, parallel-arm cluster randomized, controlled trial. Both the iNCK (intervention arm) and local standard of care (control arm) will be delivered to enrolled participants during their third trimester of pregnancy by LHWs. A total of 77 clusters, defined as union councils or sub-union councils with LHW coverage, were randomized, using covariate constrained allocation (using cluster specific estimates of NMR and proportion of health facility deliveries), to either the intervention or control arms. Union councils in Pakistan constitute district subdivisions directly involved in local government administration. These administrative divisions within the seven GB districts of interest were chosen as clusters because LHWs working within the territory of a certain union council provide services only to households within the boundaries of that union council. To obtain 77 clusters and reduce the risk of contamination, some larger union councils were further sub-divided into two or three sub-union councils, each of which was defined as a distinct study cluster based on LHW coverage (i.e., LHW(s) work only within the sub-union area and thus sub-unions could be randomized to different study arms). Union councils and sub-councils were treated as equal units when clusters were randomized to intervention or control groups. Finally, while 78 clusters were initially planned for randomization, one cluster in district Astore had to be excluded, before randomization, due to security concerns and therefore the final allocation was 39 clusters in the intervention arm versus 38 in the control arm.

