### Randomization

Covariate-constrained randomization was used to promote balance in key indicators associated with neonatal mortality between arms [26]. The randomization strategy considered: (1) cluster-level baseline NMR; (2) cluster-level baseline proportion of newborns delivered at a health facility; and, (3) GB study district (nominal categorical variable of the seven study districts). In December 2021, all clusters were randomized and allocated to either the intervention or control arm by a statistician who is not affiliated with the study, using the cvcrand package in R version 4.1.2 [27]. Balanced randomization schemes were defined as those where between-arm differences for baseline NMR were < 5%, baseline health facility deliveries were < 10%, and where at least 33% of clusters per district were allocated to each arm. The statistician then randomly selected one scheme from all balanced schemes (*n* = 11,041) using a random seed number.

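### The omphalitis and PPH models leave out two of the three covariates that constrained the randomisation; precision is lost to the extent that these predict the outcomes

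*Protocol article*

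**What the plan says.** All statements are in the Protocol article.

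- **Randomization** lists the constrained factors as "1) cluster-level baseline NMR; (2) cluster-level baseline proportion of newborns delivered at a health facility", with study district as the third. A scheme was acceptable if "between-arm differences for baseline NMR were < 5%, baseline health facility deliveries were < 10" per cent, and if "at least 33% of clusters per district were allocated to each arm". Whether the first two limits are relative differences or percentage points is not stated.
- **Study design** gives the result: "the final allocation was 39 clusters in the intervention arm versus 38 in the control arm".
- **Statistical analysis plan**, mortality model: besides individual covariates and calendar time, it includes "GB study district, log cluster-specific baseline NMRs, and the cluster-specific baseline proportion of children delivered at a health facility", and identifies these as the randomisation covariates.
- **Statistical analysis plan**, omphalitis model: "Analyses of omphalitis (secondary outcome) will adjust for newborn sex, antenatal care, and GB study district".
- **Statistical analysis plan**, PPH model: parity, maternal age, prior C-section, then "history of prior PPH, GB study district, and the cluster-specific baseline proportion of women who reported experiencing PPH".

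No reason is given for treating the secondary models differently. Both covariate lists are written out, so this is stated content and not detail left to a fuller plan.

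**The concern.** When allocation is forced to balance on a covariate that predicts the outcome, chance imbalance on that covariate is reduced. A model that omits the covariate still counts its between-cluster variation in the standard error. Two separate losses can follow. The interval is wider than an adjusted one would be, because explainable variation stays in the residual. It may also be wider than the estimate's true sampling variation warrants, so that the test rejects too rarely.

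The article itself makes facility delivery a plausible predictor. Its Background ties unsafe home delivery to non-sterile cord cutting and to harmful substances put on the umbilical stump, and says such conditions add to maternal risk. It offers no comparable argument for baseline NMR as a predictor of omphalitis or PPH.

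At stake is the chance of detecting a real effect on the two secondary outcomes that are given multivariable risk-ratio models. The pilot's omphalitis result was borderline (RR 0.68, 95% CI 0.48–0.98, p = 0.04), and misoprostol, which targets PPH, is not among the pilot kit contents listed in the Rationale.

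**Working it through.** **1. Covariate lists side by side.**

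| Constrained covariate | Mortality | Omphalitis | PPH |
|---|---|---|---|
| District | yes | yes | yes |
| Baseline NMR | yes (log) | no | no |
| Baseline facility-delivery proportion | yes | no | no |
| Cluster baseline of the outcome itself | yes (the NMR) | no | yes |

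The omission is confirmed for both secondary models.

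**2. No planned figure to reproduce.** The power, rate and intracluster correlation under Sample size concern mortality only. The rest is therefore illustrative.

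**3. Inputs.** From the article: 39 and 38 clusters, seven districts, about 306 births per cluster, the three balance limits, modified Poisson regression with robust variance, α = 0.05. Assumed: outcome risk 5%; residual between-cluster SD 0.2 on the log scale; mean facility proportion 0.62, SD 0.18; log-risk change per SD of facility proportion g = 0, −0.2 or −0.4; no effect of baseline NMR; true RR 1.0 or 0.85.

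**4. Expected standard errors by hand.** Sampling variance of a cluster's log risk is about (1 − 0.05)/(306 × 0.05) = 0.062. The allocation factor is 1/39 + 1/38 = 0.0520.

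- Facility adjusted: √[(0.04 + 0.062) × 0.0520] = 0.073.
- Facility omitted, g = −0.2: √[(0.04 + 0.04 + 0.062) × 0.0520] = 0.086.
- Facility omitted, g = −0.4: √[(0.16 + 0.04 + 0.062) × 0.0520] = 0.117.

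**5. Does the facility limit bind?** Without constraint, the between-arm difference in mean facility proportion has SD 0.18 × √0.0520 = 0.041.

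- Relative reading: 10% of 0.62 is 0.062, or 1.5 SD. About 13% of allocations are excluded on this criterion, and the variance of the difference falls to about 56% of its unconstrained value.
- Percentage-point reading: 0.10 is 2.4 SD. About 1.5% are excluded, and about 90% of the variance remains. The limit hardly binds.

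**6. Simulation (2,000 runs per setting; t reference).** Each cell gives the planned model, then the model with both covariates added.

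| Outcome and reading | g | Type I error | Power at RR 0.85 |
|---|---|---|---|
| Omphalitis, relative | 0 | 5.4% / 5.1% | 57% / 56% |
| Omphalitis, relative | −0.2 | 4.5% / 6.0% | 41% / 55% |
| Omphalitis, relative | −0.4 | 2.5% / 5.7% | 21% / 55% |
| Omphalitis, facility in points | −0.2 | 5.2% / 5.9% | 43% / 59% |
| Omphalitis, facility in points | −0.4 | 5.2% / 5.6% | 25% / 55% |
| PPH, relative | −0.2 | 4.2% / 5.3% | 48% / 58% |
| PPH, relative | −0.4 | 3.7% / 6.1% | 36% / 59% |

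The PPH rows include a simulated cluster baseline PPH proportion in both models. The simulated omphalitis standard errors under the null (relative reading) were 0.087 planned against 0.074 adjusted at g = −0.2, and 0.122 against 0.073 at g = −0.4, close to step 4. Under the relative reading with a prognostic covariate, the planned omphalitis standard error exceeded the true sampling SD by 3% to 13%. Under the percentage-point reading, planned coverage under the null was 94.8% at both values of g.

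The Monte Carlo standard error of a 5% rejection rate is √(0.05 × 0.95/2,000) = 0.5 points, so 6.0% and 6.1% lie about two standard errors above nominal.

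**The case against.** A reader might infer that the planned intervals are certainly too wide and that power is certainly lost. The article does not support that. It shows no relation of either covariate to omphalitis or PPH after the retained covariates, and where there is none the two analyses perform alike. Intervals wider than their own sampling variation also require limits that bind. The quantity being limited is itself a percentage, so percentage points is a natural reading, and coverage is then about nominal. This objection stands: the point is conditional.

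The size can also be exaggerated. Much of the variation in cluster results is sampling noise that no cluster covariate explains. If the mortality correlation of 0.002 is borrowed for illustration, true between-cluster variance is only 306 × 0.002/(1 + 305 × 0.002) = 0.612/1.61 = 38% of the variance of a cluster mean. For PPH, the outcome's own baseline level is already in the model and recovers part of the loss. Both limits stand.

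Outcome-specific covariates are defensible, these are secondary outcomes, and omission errs on the conservative side. That lowers the priority but does not explain why the design covariates are used in one model and dropped from two. Adjustment is also not wholly free: simulated type I error reached 6.1%, which argues for a small-sample correction.

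Finally, a reader might extend the point to the regression comparing care-seeking between arms. The article lists no covariates for that regression, so no omission is stated there.

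**Conclusion.** The point holds in conditional form. Two of the three covariates that constrained the allocation are missing from the omphalitis and PPH models, although the mortality model includes all three. That much is certain from the text.

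The consequence depends on two things that the article does not settle:

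- **Prognostic strength.** If the covariates do not predict the outcome, nothing is lost. If facility delivery does, precision and power fall under either reading of the limits. The illustrative loss is 14 to 16 power points for omphalitis (41% against 55%; 43% against 59%) and 10 for PPH (48% against 58%) at g = −0.2, and larger at −0.4.
- **Tightness of the limits.** On the relative reading the tests are also conservative, with type I error of 2.5% to 4.5% in the prognostic settings. On the percentage-point reading coverage stays about nominal and only precision is lost.

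These figures rest on the assumed 5% risk, residual SD of 0.2, facility distribution and values of g. They show direction and plausible scale and do not forecast this trial. Because the simulation gave baseline NMR no effect, the gains come from facility delivery alone. The mortality analysis and its conclusion are untouched.

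**What to change.** Before outcome analysis, add cluster-specific baseline NMR and the cluster-specific baseline facility-delivery proportion to both the omphalitis and the PPH model, alongside district, as in the mortality model. Keep the baseline PPH term in the PPH model. In the same revision, state whether the 5% and 10% balance limits were relative or in percentage points, so that readers can judge how tightly they bound.

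The log form of NMR is undefined for any cluster with no recorded baseline deaths. The article does not say whether there is one, so choose a scale that accommodates zero if needed.

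The cost is a change of wording and two cluster-level degrees of freedom out of 77 clusters. No new data are required, since the baseline survey covered all 77 clusters and supplied both quantities for the randomisation. Specify a small-sample correction to the robust variance, or a t reference distribution, with the added terms.
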